
### Data management and monitoring

2.7

Data management will be done by the Telehealth Center of UFMG's University Hospital. Data entry will be made through a password-protected, web-based interface by a registered team and double-checking for verification of data consistency will be performed. The study's steering committee ([name], [name], [name]) has the overall responsibility for the conduction and periodic monitoring of the study.

### Statistical methods

2.8

Analysis will be performed according to the intention-to-treat principle. For the baseline characteristics, continuous variables will be summarized as mean ± SD or as median and first and third quartiles (Q1, Q3), and groups compared using Student *t* tests or Mann–Whitney test, based on the distribution pattern. Categorical variables will be expressed as proportions and 95% CIs and groups compared by Chi-square test. The primary outcome will be compared between groups using Chi-square test. We will also analyze effects across subgroups, such as sex, age, or other covariates of interest, using logistic regression models. The criterion for statistical significance will be set at α = 0.05 and SPSS Statistics for Windows (Version 20.1; IBM Corp., Armonk, NY) will be used for the analysis.

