### Interventions

2.2

The usual care group (IMPACS control group) will receive standard discharge treatment and standard hospital follow-up. They will monthly receive text messages thanking for their participation in the trial and reminders of trial appointment.

The intervention group (IMPACS intervention group) will receive the usual post-discharge care for ACS, instructions and information, as well as the SMS intervention program. The SMS program will include a variety of topics, such as standard follow-up care reminders and general self-management and healthy habits texts to inform and engage patients in care. The Intervention will run for 6 months and the program will consist of 4 modules, according to baseline characteristics of participants:

(1)Module 1: nonsmokers and free of diabetes;(2)Module 2: nonsmokers and diabetic patients;(3)Module 3: smokers and nondiabetic patients;(4)Module 4: smokers and diabetic patients.

Modules 2 and 4 are subdivided into 2 according to whether or not diabetic patients are in use of insulin. Texts will be sent out 4 times per week for 180 days at pre-established times, with the first SMS being sent immediately after hospital discharge. All participants included in the same module will receive the same texts and in the same order, regardless of the allocation time in the study. No cross-over between groups is expected.

All participants will also be followed by the UFMG's University Hospital Coronary Artery Disease outpatient clinic and rehabilitation program, unless they choose otherwise. IMPACS researchers will be independent of attending physicians and will not interfere with patient care.

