### Outcomes

2.3

Participants will have outcomes measured at 6 months (±1 month) after hospital discharge, in the follow-up appointment pre-scheduled by the study's researchers. Researchers blinded to treatment allocation will collect the data.

(1)Primary endpoint: The primary outcome is achieving 4 or 5 points in a risk factor control score, which combine the cluster effect of 5 main modifiable risk factors for ACS [low-density lipoprotein cholesterol - LDL-C <70 mg/dL, blood pressure <140/90 mm Hg, regular exercise (≥5 days/week × 30 minutes of moderate exercise per session), nonsmoker status, and BMI <25 kg/m^2^].(2)Secondary endpoints: Plasma LDL-C levels, objective level of physical activity, blood pressure, medication adherence, proportion of nonsmokers, BMI, death from any cause, rehospitalization, and cardiovascular death.

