**Table 3 T3:**
[figure not shown]
Flow chart of study design.

The data collection protocols are briefly summarized in the following:

(1)Plasma LDL-C level: measured at baseline and 6 months after hospital discharge (before the outpatient appointment), after 12 hours of fasting, in the same laboratory. Measurement of total cholesterol, triglycerides, and high-density lipoprotein cholesterol will be done with CHOL VITROS Chemistry Products slides from Ortho Clinical Diagnostics (VITROS 5.1 and VITROS 5.600/colorimetric method). For LDL-C dosage, the value is generally calculated. When triglycerides value >400 mg/dL, we will perform direct dosing of LDL-C using the reagent LDL VITROS Chemistry Products from Ortho Clinical Diagnostics (VITROS 5.1 and VITROS 5.600 / End point Method).(2)Level of physical activity: measured by the International Physical Activity Questionnaire Short Form (IPAQ-SF) ^[20]^ at baseline and 6 months after hospital discharge. The measure will be validated in one-fifth of the participants by using accelerometers (Actigraph wGT3X-BT; Pensacola, FL). A question about whether the patient is performing scheduled physical activity following the recommendation of the Brazilian Society of Cardiology will also be included in the follow-up questionnaire.^[21]^(3)Blood pressure: measured at baseline and 6 months after hospital discharge by the same automatic blood pressure device (OMRON model HEM-705 CP Intellisense) and OMRON blood pressure cuffs up to 48 hours before hospital discharge and in the follow-up visits. Three resting measurements will be made, with the patient in the seated position, with the arm supported. The mean of the last 2 readings will be considered for data analysis.(4)Medication adherence: measured at 6 months after hospital discharge via “Medida de Adesão aos Tratamentos” – MAT,^[22]^ a validated instrument composed of 6 items that evaluate the behavior of the individual in relation to daily use of medicines. The answers are obtained by means of a 6-point ordinal scale that varies from “always” [1] to “never” [6]. The values obtained with the answers to the 6 items are summed and divided by the number of items (values vary from 1 to 6). Subsequently, values 5 and 6 are computed as 1 (adherent) and the others are computed as 0 (nonadherent).(5)Proportion of nonsmokers: measured at 6 months after hospital discharge by self-report. The participant will answer the following question: “Are you smoking after hospitalization?”, for which he/she could answer “Yes” or “No.” The answer will be also confirmed by a Carbon Monoxide Meter Breath Test (piCO Smokelyzer, Kent, UK). This is an indirect and noninvasive measure of blood carboxyhemoglobin. The device directly measures carbon monoxide (ppm) and carboxyhemoglobin is a calculation based on clinical evidence. The values obtained by the device are 0 to 6 (nonsmoker range), 7 to 19 (light smoking range), and 20 or more (heavy smoking range).^[23,24]^(6)BMI: measured at baseline and 6 months after hospital discharge. BMI will be calculated by weight measured in kilograms divided by height in square meters.(7)Rehospitalization: measured at 6 months by means of self-report and medical discharge records.(8)Cardiovascular death and death from any cause: measured at 6 months by report of relatives and confirmed by death certificate or medical records.(9)Health literacy questionnaire: measured at baseline. A version consisting of 18 items of The Short Assessment of Health Literacy for Portuguese speaking Adults (SAHLPA-18) ^[25]^ will be applied to participants at the baseline.(10)Follow-up questionnaire: a follow-up questionnaire with self-report of reading messages will be applied as well as questions about acceptability and understanding (Appendix 3).

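### The primary test is an unadjusted chi-square although baseline values of the score components are available: a modest loss of precision, not an error

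*Protocol article*

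**What the plan says.** Section 2.3 of the protocol article defines the endpoint: "The primary outcome is achieving 4 or 5 points in a risk factor control score". The score counts five targets at 6 months: LDL-C, blood pressure, exercise, nonsmoking and BMI.

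Section 2.8 fixes the comparison: "The primary outcome will be compared between groups using Chi-square test". Regression appears only for another purpose: "We will also analyze effects across subgroups, such as sex, age, or other covariates of interest, using logistic regression models". The article gives no covariate-adjusted comparison of the primary outcome.

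Four of the five components have a baseline measurement in section 2.6:
- LDL-C: "Plasma LDL-C level: measured at baseline and 6 months after hospital discharge".
- Activity, by IPAQ-SF: "at baseline and 6 months after hospital discharge. The measure will be validated in one-fifth of the participants by using accelerometers".
- Blood pressure: "Blood pressure: measured at baseline and 6 months after hospital discharge by the same automatic blood pressure device".
- BMI: "BMI: measured at baseline and 6 months after hospital discharge".

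For the fifth, smoking, section 2.6 lists a 6-month measurement only. Status at entry is implied by section 2.2, where "the program will consist of 4 modules, according to baseline characteristics of participants", the modules being split by smoking and diabetes. Section 2.5 describes 1:1 randomisation in blocks of four by enrolment date and names no stratification factor.

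**The concern.** The outcome is whether a patient meets at least four of five targets at 6 months, and the same quantities are recorded at entry. If a patient's status at entry predicts status at 6 months, an analysis that ignores it leaves explainable variation in the error term. Randomisation does not balance these factors beyond chance, so neither the design nor the primary analysis uses them.

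Two things are at stake. The first is efficiency: the trial plans for 80% power and has little to spare. The second is how the result reads if the arms happen to differ at entry on a prognostic component. A crude test cannot account for such a difference, and an adjustment chosen after seeing it would be open to challenge.

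**Working it through.** **Inputs from the protocol article.** Two-sided 5% level, 80% power, a difference of 19 points (read as absolute), 141 evaluable patients, 160 enrolled, 15% loss (section 2.4); 1:1 allocation (section 2.5).

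**Inputs not in the documents.** The control rate, the prevalence of each component, and how strongly baseline predicts the outcome. All are assumed below.

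**1. The plan's own figure.** The pooled-variance formula for two proportions, with control rate 0.11, intervention rate 0.30 and mean 0.205, gives per arm

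[(1.96 × √(2 × 0.205 × 0.795) + 0.8416 × √(0.11 × 0.89 + 0.30 × 0.70)) / 0.19]² = [(1.119 + 0.467) / 0.19]² ≈ 69.7, so 70 per arm and 140 in total.

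The stated 141 can therefore be matched at a control rate of about 11%, but not verified; a rate of about 70% matches equally well. The low rate is used below as an assumption.

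**2. Patients and events.** 160 × 0.85 = 136 evaluable, or 68 per arm. Expected events: 68 × 0.11 + 68 × 0.30 = 7.5 + 20.4 ≈ 28.

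**3. Chance imbalance.** For a binary factor of prevalence 30%, the SD of the between-arm difference is √(2 × 0.3 × 0.7 / 68) = 0.079, or about 8 points. The chance of a difference of 10 points or more in one such factor is:

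| Prevalence | 70 per arm | 80 per arm |
|---|---|---|
| 20% | 13.9% | 11.4% |
| 30% | 19.7% | 16.8% |
| 50% | 23.7% | 20.6% |

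An imbalance does not pass to the result one for one. As an illustration, suppose patients with and without the factor differ in outcome risk by 20–40 points (assumed). A one-SD imbalance then shifts the observed risk difference by 0.079 × 20 = 1.6 to 0.079 × 40 = 3.1 points, against a target of 19.

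**4. Validity of the chi-square.** Under no effect, exact enumeration at 68 per arm with control rates of 10–12% gives 4.9–5.1% rejections. Simulation at a 20% rate gives 4.8–5.1%. The planned test holds its level.

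**5. Gain from adjusting for the baseline score.** Simulation used 70 per arm, a control rate of about 12%, a 19-point effect, and logistic regression with a likelihood-ratio test and a standardised risk difference. Three assumed levels of persistence were tried:

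| Correlation of baseline score with outcome | Power, chi-square | Power, adjusted | Fall in variance |
|---|---|---|---|
| 0.17 | 80.4% | 82.5% | 3.2% |
| 0.24 | 80.7% | 83.2% | 6.3% |
| 0.31 | 80.4% | 85.9% | 11.8% |

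In patients, 140 × (1/0.968 − 1), 140 × (1/0.937 − 1) and 140 × (1/0.882 − 1) correspond to about 5, 9 and 19 extra evaluable patients.

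**6. Sensitivity.**
- Adjusting for baseline score and BMI at N = 136 with strong BMI persistence (assumed latent correlation 0.95), using a linear risk-difference model as a stand-in for the logistic one, cut the SD from 0.0672 to 0.0629, or from 0.0675 to 0.0647 with lower persistence of other components. The variance falls are 1 − (0.0629/0.0672)² = 12% and 1 − (0.0647/0.0675)² = 8%. Power rose from about 80.6% to 83.5%.
- With BMI correlation 0.8 and smoking 0.5, the gain was 0.7 power points and 5% of variance.
- A further run under assumed inputs gave 6–13% of variance and about 4–6 power points.
- With a covariate of no prognostic value and a control rate of 10%, power was 82.8% with and without adjustment.

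**7. Level of the adjusted test.** At a 20% rate under no effect, the likelihood-ratio test rejected in 5.1% and 5.6% of runs as prognostic strength rose. The inflation is slight, but with about 28 events the choice of test matters.

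**The case against.** The strongest reply is that nothing here is wrong. The chi-square suits a 1:1 randomised comparison of proportions, matches the difference on which the sample size rests, and holds its level. Chance imbalance is already part of that 5%. This stands in full. A reader might infer from the missing adjustment that the primary result would be biased or the test invalid; the documents do not support that. The loss is in precision, and in conditional accuracy once an imbalance has occurred.

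The second reply is that the gain is small and rests on undocumented inputs. This also stands. The control rate was back-solved from the sample size and the correlations are assumed. A reader might infer that much of the 6-month result is settled at entry, but no section shows this. Baseline blood pressure is an in-hospital reading up to 48 hours before discharge, in a patient admitted for ACS, and may predict 6-month control only moderately. Persistence is more plausible for BMI and smoking, two components of five.

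The third reply is that the baseline score is not fully in hand. Section 2.6 measures smoking, with breath carbon monoxide confirmation, at 6 months only. Entry status is inferred from the modules, which section 2.2 describes for the intervention programme. Baseline questionnaires (section 2.2.2) and baseline clinical characteristics (section 2.6) make it likely that smoking is recorded in both arms, but the article does not say so. It is therefore too strong to say that every item needed is already collected.

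None of this gives a reason to prefer the crude test as primary when four components are measured at baseline in any case.

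**Conclusion.** The point holds as an efficiency and robustness weakness in a valid analysis. Section 2.8 fixes an unadjusted primary test, and neither the randomisation nor that test uses the baseline components.

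The direction of the gain is well supported; its size is not. At an assumed control rate near 10–12%, a reasonable range is 3–13% lower variance and about 1–6 power points, and nil if baseline does not predict the outcome. The change is worth making because it costs almost nothing and removes discretion over later adjustment. The trial does not depend on it.

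The point concerns the primary comparison only. A reader might extend it to baseline-adjusted models for the secondary endpoints, but an article commonly leaves those methods to the full plan. A reader might also object to the planned tests of baseline differences, but dropping them would change no result.

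**What to change.** Reword section 2.8, before outcome data are seen by arm, along these lines:

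- **Primary analysis:** logistic regression of reaching 4–5 points on arm, baseline number of controlled factors (0–5) and baseline BMI. With about 28 events this means three coefficients besides the intercept, or roughly nine events each (28/3 ≈ 9.3), so add no more covariates.
- **Reported effect:** the standardised (marginal) risk difference with 95% CI, which keeps the scale used for the sample size.
- **Test of arm:** one that is robust or adequate in small samples, for example a robust-variance test of the standardised risk difference or a re-randomisation test that respects the blocks. An uncorrected likelihood-ratio test should not be relied on.
- **Supportive analysis:** the chi-square test as now planned.
- **Baseline score:** define each item, taking smoking from the status used for module assignment, and confirm that this status is recorded before allocation in both arms.

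The endpoint, sample size and visit schedule stay as they are. The cost is slightly more analysis work. The planned software fits the logistic model; the standardised risk difference and its interval may need an extra step.

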### Ethics and dissemination

2.9

Patients will be asked if they wish to participate in the study while hospitalized. After screening for inclusion and exclusion criteria, eligible patients will receive written an oral information about the study. Written and informed consent will be obtained from all participants before allocation. The ethical approval for this study has been obtained from The Medical Ethics Committee of the Universidade Federal de Minas Gerais (Number: 2,054,294 dated August 03, 2017). Any changes in the protocol during the trial that may affect the conduct of the trial, safety, and the benefit to patients will require a formal amendment to the initial protocol and be immediately communicated to The Medical Ethics Committee. The findings of this study will be published and disseminated via scientific forums, with no restrictions.

## Discussion and conclusion

3

The “IMPACS” study is an innovative study, as it evaluates the implementation of an effective and simple strategy in the secondary prevention of CVD in a middle-income country. Two important issues make this study different from others who used SMS as a telehealth tool: the range of approaches and the measurement of health literacy.

The messages address several essential conditions for CVD prevention at the same time: medication adherence, regular physical exercise, healthy dietary habits, smoking cessation (if appropriate), diabetes management (if appropriate), and general information on coronary heart disease, all of them with a language adapted to cultural and social level of the target population. In order to compare the results of the IMPACS study with those found in previous studies of SMS intervention in high-income countries, the assessment of health literacy is a crucial factor.

In conclusion, the IMPACS study aims to provide information, by randomized controlled data, whether SMS interventions is effective in increasing CVD risk factors control in patients post-ACS in a middle-income country.
